### 2.3. Data Management

All data will be pseudo-anonymized and stored on a secure Research Electronic Data Capture (REDCap^®^, Vanderbilt University, Nashville, TN, USA) platform hosted by the Fondazione IRCCS Policlinico San Matteo in Pavia. Only authorized study staff will have access. Data collected will include demographic data (age, sex, etc.); OHCA- and resuscitation-related variables (time to ROSC, initial rhythm, neurological outcome); scores from MoCA, HADS, EQ-5D-5L, and IES-R at each time point, and qualitative information collected in the semi-standardized follow-up interviews.

### 2.4. Statistical Methods

Baseline characteristics will be reported as means ± SD, or medians [IQR] for continuous variables, and as frequencies (%) for categorical variables. Prevalence of psychological distress, cognitive impairment, fatigue, symptoms of post-traumatic stress, and reduced quality of life will be estimated at all timepoints; exact 95% confidence intervals will be calculated. Reduced quality of life will be defined as an EQ-5D-5L VAS score at least 7 points lower than the age-matched Italian general population mean [26], based on established minimal clinically important differences identified in chronic disease populations [27,28].

Incidence rates (expressed per 100 person-years) for mood disorders, post-traumatic stress symptoms, reduced quality of life, and cognitive impairment will be calculated for participants free of the respective condition at baseline. Incident cases will be defined as follows: a HADS subscale score > 8 for mood disorders (either anxiety or depression subscale), IES-R ≥ 33 for post-traumatic stress symptoms, a MoCA score < 26 for cognitive impairment, and a decrease of ≥7 points from the age-matched normative mean on the EQ-5D-5L VAS for reduced quality of life. Baseline status will be determined using the initial T0 assessment; if T0 data are missing, the T1 (1-month) assessment will be used. Participants with missing data at both T0 and T1 for a given outcome will be excluded from the incidence rate calculation for that outcome. Incidence rates will be reported with exact 95% confidence intervals.

Longitudinal changes in HADS, MoCA, EQ-5D-5L, and IES-R from T0 to T4, as well as differences in the retention rate between patients seen remotely or face-to-face, will be analyzed using mixed-effects models (linear or logistic) incorporating time and potential covariates (e.g., age, sex, comorbidities). Models will initially include random intercepts and slopes at participant and hospital levels. Different residual covariance structures (e.g., first-order autoregressive [AR(1)]) will also be explored. Model selection will be guided by the Akaike Information Criterion (AIC) and Bayesian Information Criterion (BIC); simpler random intercept-only models will be adopted if convergence issues arise. Missing data will be handled using Multiple Imputation by Chained Equations (MICE), assuming a Missing At Random (MAR) mechanism. Twenty imputed datasets will be generated, incorporating all key predictors and outcomes, as well as hospital ID. Participants who completely withdraw from this study will be treated as censored at their last observation without further imputation. Sensitivity analyses comparing complete-case and imputed datasets will be conducted to assess the robustness of the findings. A *p*-value < 0.05 (two-sided) will denote statistical significance.

Qualitative data will be derived from detailed notes taken during semi-structured interviews; the analysis will employ a framework approach, well-suited for applied qualitative research with pre-defined areas of inquiry [29]. The analytic process will involve familiarization with the notes, followed by the development of a thematic framework based on the predetermined domains. Data will then be indexed using both deductive codes—stemming from the interview guide—and emergent codes that may arise from the content of the notes. A matrix will be constructed to chart responses across cases, enabling systematic cross-case comparisons.

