During 2017–2018, the Cardiology Division of the Fondazione IRCCS Policlinico San Matteo, which is the coordinating centre of the Lombardia Cardiac Arrest Registry (LombardiaCARe), in collaboration with a non-profit organization (Pavia nel Cuore ODV) and the Psychiatry Unit of the University of Pavia, promoted a pilot study on the assessment of the psychological and emotional state of out-of-hospital cardiac arrest survivors in the Province of Pavia. This project showed that, in line with international data, more than one-third of patients discharged with a good neurological outcome (mRS ≤ 3) showed symptoms of at least moderate depression [18]. The incidence of depression was also higher in younger patients (<50 years old), in line with other observational studies [19,20,21], with mental health being particularly affected. The health-economic implications of this long-term burden are likely significant.

Building on those pilot data, this study aims to (a) investigate the feasibility and acceptability of a centralized, sub-regional assessment and follow-up system; and (b) to investigate the prevalence of psychological distress, cognitive impairment, and fatigue, as well as the degree of health-related quality of life in a large, multicentre cohort of OHCA survivors.

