## 2. Materials and Methods

### 2.1. Study Design

This is a prospective, multicenter observational protocol, spanning 24 months, across 22 hospitals affiliated with the Lombardy Cardiac Arrest Registry (“Lombardia CARe”—a full list of the hospitals is provided in Table 1). This network covers a population of approximately 4.3 million people and includes densely populated urban areas and sparsely populated rural and mountainous locations.

In the REVIVE project, each of the 22 hospitals will have a named contact person (usually a senior cardiologist) who will enroll eligible survivors and inform the study team of the clinical status and readiness to be assessed before hospital discharge. Based on registry data from 2022, >90% of patients with a good neurological outcome (CPC 1–2; mRS ≤ 3) were discharged from 11 hospitals affiliated to this network, therefore these sites have been highlighted in Table 1 as ‘Main Recruiters’ and a picture describing their approximate location in the Lombardy region is provided (Figure 1).

The REVIVE project plans to enroll consecutive OHCA survivors meeting eligibility criteria and to follow them up for 12 months post-discharge. Survivors will be assessed at five different timepoints: **T0**—before discharge (or within 15 days post-discharge); **T1**: 1 month post-discharge; **T2**: 3 months post-discharge; **T3**: 6 months post-discharge; **T4**: 12 months post-discharge.

At each time point, the same battery of questionnaires will be administered **in-person or over the telephone/via telemedicine**, based on patient preference and feasibility.

Should a significant need be identified, the study team will, in the first instance, consider whether psychological therapy/cognitive rehabilitation can be provided in-house; however, it is expected that most patients will be referred to community-based rehabilitation programmes or other specialists where required.

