#### 2.1.3. Enrolment and Assessments

The Lombardia CARe Registry records all admissions of patients who have suffered an out-of-hospital cardiac arrest across seven provinces in the Lombardy region, updated to the previous 24 h. This registry is monitored daily by the team involved in this study; for patients admitted to the IRCCS Policlinico San Matteo Hospital in Pavia, their clinical history (including survival and neurological status) is monitored via the hospital internal electronic system and, if eligible, they are approached to provide consent for participation to this study close to their discharge day, usually in the cardiology ward. For those patients admitted to one of the ten other main recruiting hospitals (Figure 1), the local investigator will approach them for screening and enrollment. They will also inform the study team about their clinical status and readiness for assessment before hospital discharge. To minimize the risk of patients being missed, an email will be sent to all the investigators of the main recruiting hospitals every Monday and every Friday. The secondary recruiting centres do not have an allocated local investigator, so they will be contacted as and when required.

Most eligible patients are supposed to be approached before hospital discharge; if not, the study management team will contact them within 15 days post-discharge. Following informed consent, baseline assessment will be conducted by a clinical psychologist, either in-person (for patient admitted to Fondazione IRCSS San Matteo hospital, Pavia) or remotely (via telephone call or telemedicine, for all other patients), using measures of cognitive ability (Montreal Cognitive Assessment [22]), anxiety and depression [23], health-related quality of life [24], and symptoms of post-traumatic stress disorder [25]. Parallel versions of the cognitive assessment will be administered to reduce practice effects. A list of all measures and their purpose is described in Table 2.

In addition to quantitative instruments, starting from the first follow-up after hospital discharge (that is, the 1-month follow-up), patients will also undergo a brief semi-structured, qualitative interview focused on their own subjective experience of returning to day-to-day life, fatigue, cognitive problems, mood difficulties, and their ability to access appropriate information/support about their condition (Appendix A; Table A1).

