## Appendix A

**Table A1 jcm-14-03631-t0A1:** Semi-structured clinical interview for post-cardiac arrest survivors.

Semi-Structured Clinical Interview (English Translation)
**Cognition and Cognitive Functions:** *“Have you noticed any changes in your memory, ability to concentrate, or finding the right words after being discharged? How have these changes affected your daily activities?”* 2. **Emotional Well-Being and Mood:** *“In the past few weeks, have you experienced feelings of anxiety, low mood, or unwanted memories related to the cardiac arrest? How have these feelings impacted you or your family members?”* 3. **Fatigue and Physical Recovery:** *“Do you experience persistent fatigue, mobility difficulties, or physical limitations that make daily activities more challenging compared to before the cardiac arrest?”* 4. **Daily Life, Work, and Independence:** *“Have you encountered difficulties in resuming important daily activities, such as driving, managing household tasks, or returning to work? Do you feel you have the necessary support to face these challenges?”* 5. **Information Needs and Support Networks:** *“Do you and your family feel you have the necessary information and support—for example, understanding medication use, knowing what to expect in the coming months, and accessing emotional or peer support—to manage this phase of recovery effectively?”*

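### Fatigue prevalence is promised at all timepoints, but no fatigue data are planned at T0, and from T1 the only source is a compound interview item with no case definition

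*Protocol article*

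**What the plan says.** **The promise.** The second aim in the Introduction is "to investigate the prevalence of psychological distress, cognitive impairment, and fatigue", together with health-related quality of life. Section 2.4 turns this into an analysis: "Prevalence of psychological distress, cognitive impairment, fatigue, symptoms of post-traumatic stress, and reduced quality of life will be estimated at all timepoints", each with an exact 95% confidence interval. Section 2.1 defines five timepoints. T0 falls "before discharge (or within 15 days post-discharge"), and T1 to T4 fall at 1, 3, 6 and 12 months.

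**The data.** Section 2.1 adds: "At each time point, the same battery of questionnaires will be administered". Section 2.1.3 describes the baseline assessment as "using measures of cognitive ability (Montreal Cognitive Assessment [22]), anxiety and depression [23], health-related quality of life [24], and symptoms of post-traumatic stress disorder [25"], and presents Table 2 as listing every measure. Table 2 contains MoCA, HADS, EQ-5D-5L and IES-R. Section 2.3 says the database will include "scores from MoCA, HADS, EQ-5D-5L, and IES-R at each time point, and qualitative information collected in the semi-standardized follow-up interviews".

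**Where fatigue is asked about.** Section 2.1.3 says that "starting from the first follow-up after hospital discharge (that is, the 1-month follow-up), patients will also undergo a brief semi-structured, qualitative interview", and names fatigue among its topics. The corresponding question in Appendix A, Table A1 (item 3 of the English translation) reads: "Do you experience persistent fatigue, mobility difficulties, or physical limitations that make daily activities more challenging compared to before the cardiac arrest"?

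**The concern.** A prevalence with an exact binomial interval needs a yes/no case status for each patient at each timepoint. For the other outcomes the article supplies an instrument and a threshold. For fatigue it supplies neither, and the one place where fatigue is discussed with the patient is absent from the first timepoint.

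At stake is one of the three conditions named in the prevalence aim. The Discussion expects the results to guide recommendations on follow-up services. A fatigue figure that has no baseline value, and that may include patients whose difficulty is mobility or another physical limitation, would be weak support for that. Data not collected at T0 cannot be recovered later for patients already assessed.

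**Working it through.** The point rests on no sample size, power or error rate, and the article gives no fatigue figure to reproduce. The check sets the promise beside the planned data.

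**1. Is fatigue measured by the battery?** By the purposes stated in Table 2:

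| Instrument | Stated purpose | Fatigue? |
|---|---|---|
| MoCA | cognitive deficits | no |
| HADS | anxiety and depression | no |
| EQ-5D-5L | mobility, self-care, usual activities, pain/discomfort, anxiety/depression, plus overall health on the VAS | no |
| IES-R | post-traumatic stress symptoms | no |

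That is 0 of 4. Because section 2.1 uses one battery throughout, no fatigue questionnaire is added later.

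**2. Is there a case definition?** Sections 2.4 and Table 2 give HADS subscale > 8, IES-R ≥ 33 and MoCA < 26. Section 2.4 also gives EQ VAS at least 7 points below the age-matched norm. That makes four thresholds, none for fatigue. Fatigue is also absent from the incidence outcomes in section 2.4 and from the scores to be modelled over time. This is what one would expect if no fatigue variable exists.

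**3. What exists at each timepoint?**

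| Timepoint | Battery includes fatigue | Interview held | Fatigue information |
|---|---|---|---|
| T0 | no | no | none |
| T1, T2, T3, T4 | no | yes | notes on one compound question |

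So 1 of 5 timepoints has no fatigue information, and 4 of 5 have interview notes only. The multiple imputation in section 2.4 cannot fill T0: fatigue would be observed there for nobody, so the study holds no information on its T0 distribution.

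**4. What can the notes yield at T1 to T4?** Section 2.4 plans detailed notes, codes taken from the interview guide and arising from the content, and a matrix of responses across cases. A per-patient fatigue code, and hence a crude proportion, could be drawn from that matrix. Two things are not fixed: which answer makes a patient a case, and whether the interviewer must note separately which of the three difficulties the patient has. Where the notes do not separate them, the code cannot either. The Italian original joins the same three elements (numbered 4 there, because the first question is printed twice), so the compound wording is not a product of translation.

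**5. How large could the mixing be?** The documents give no frequency for fatigue, for mobility or physical limitation, or for their overlap. If every patient with such a limitation is also fatigued, nothing is added. If some are not, and are coded as cases, the estimate is too high by their share. No figure can be put on this from the documents.

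**The case against.** A reader might infer that fatigue prevalence cannot be estimated at any timepoint. The documents do not support that for T1 to T4. Section 2.1.3 names fatigue as an interview topic in its own right, apart from cognition and mood, and the planned notes, codes and matrix could give a crude proportion.

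A reader might also infer that every yes to the compound question will be counted as fatigue, so that the estimate must be inflated. Nothing in the article says the item is scored as a tick-box. It is a prompt in a semi-structured interview, and good notes may show which difficulty was meant. This stands too: mixing is possible, not certain. Nor can it be measured against the 5% precision in section 3.2, which is set for anxiety or depression at 6 months. No precision target is set for fatigue.

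A further argument is that an article condenses. Table 2 is captioned as key tools, the database sentence says what will be included, and coding rules for interview data may sit in a fuller document. This softens the criticism about the case definition. It is weakened because section 2.1.3 calls the same table a list of all measures, and because the article does give thresholds for the other outcomes. It does not touch T0: an analysis plan can define a case, but it cannot create data from an interview that is not held.

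Finally, the reach is limited. Feasibility, acceptability, the sample-size statement, the incidence rates and the longitudinal models do not depend on fatigue.

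**Conclusion.** The point holds in this form. The article promises a fatigue prevalence at T0 that its own data collection cannot supply. At T1 to T4 an estimate is possible, but it has no fixed case definition and comes from a question that joins fatigue with two other problems. An exact interval there would attach to a quantity the plan has not defined.

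The size, by count: one of five prevalence outcomes, one of five timepoints with no data, and four of five resting on interview notes. The amount of mixing at those four is unknown.

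The conclusion assumes that Table 2 is the full list of measures, as section 2.1.3 says, and that the interview is not held at T0, as the same section says. If a fuller document adds a fatigue measure at T0, the article should name it.

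**What to change.** **Preferred, with no new instrument:**
- Split the question, in the Italian original as well as the translation, so that fatigue is asked alone and its answer coded yes/no at each interview. Ask about mobility and physical limitations separately.
- Add a yes/no fatigue field to the database.
- In section 2.4, remove fatigue from the all-timepoints sentence and state that the prevalence of self-reported fatigue will be estimated at T1 to T4, with exact 95% intervals. Word aim (b) to match.
- For interviews already held with the compound question, code fatigue only where the notes record it explicitly, and say how many could not be classified.

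**Otherwise:** remove fatigue from the quantitative prevalence aim and outcomes, and report it as a qualitative theme from T1.

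**Optional alternative:** add a brief fatigue scale with a fixed cut-off to the battery at T0 to T4. This is the only route to a T0 estimate, and only for patients assessed after it is introduced. It adds some patient burden.

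The preferred change costs one extra question, one database field and a few lines of text. The second costs only text.

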### 3.2. Identification of Prevalence of Mood Disorders in OHCA Survivors

Based on Lombardia CARe figures, approximately 5200 OHCAs occur yearly in the regional area, and, in about 3500 of them, resuscitation is attempted. Of these, about 600 survive to hospital admission, and about 175 per year are discharged alive with CPC 1–2 or mRS ≤ 3. Therefore, over 24 months, about 350 eligible survivors are expected. Assuming 80% of them consent to be included in this study (about 280), this cohort will be sufficient to identify the presence of symptoms of at least mild anxiety or depression in 25% of cardiac arrest survivors at 6 months from the event, with 5% precision and 95% confidence (Appendix A, Table A2). Although the prevalence of mood disorders after OHCA has been investigated by several studies, REVIVE will be the first one to do so at the sub-regional level in Italy.

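### A 7-point minimal important difference is used as an individual cut-off below the age-norm mean, with no norm comparator, so raw prevalence of reduced quality of life cannot be read as burden due to cardiac arrest

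*Protocol article*

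**What the plan says.** All the relevant rules are in section 2.4 (Statistical Methods) of the protocol article.

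- **Prevalence.** "Reduced quality of life will be defined as an EQ-5D-5L VAS score at least 7 points lower than the age-matched Italian general population mean". The threshold is said to be "based on established minimal clinically important differences identified in chronic disease populations".
- **Incidence.** Rates "will be calculated for participants free of the respective condition at baseline". For this outcome an incident case is "a decrease of ≥7 points from the age-matched normative mean on the EQ-5D-5L VAS for reduced quality of life". The reference is the population mean, not the patient's own T0 score.
- **Reporting.** Prevalence of several conditions is planned, ending with "reduced quality of life will be estimated at all timepoints; exact 95% confidence intervals will be calculated". No expected share in the norm population is named as a comparator, and no SD or percentile of the norm is given.
- **Other use of the instrument.** The same section plans mixed models for "Longitudinal changes in HADS, MoCA, EQ-5D-5L, and IES-R from T0 to T4".

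**The concern.** A minimal important difference says how large a change, or a difference between group means, has to be before it matters. It does not say at what score a person has reduced quality of life. A line drawn a short way below a population mean labels as cases everyone in the lower part of the ordinary distribution. How many that is depends on how widely scores vary between people, which the rule ignores.

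The other case rules in section 2.4 (HADS subscale above 8, IES-R of 33 or more, MoCA below 26) are fixed cut-offs on the instrument. Only the quality-of-life rule is placed relative to a population mean.

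At stake is part of aim (b) in the Introduction, which covers the degree of health-related quality of life in survivors. The Discussion expects the results to guide recommendations on follow-up services. A proportion reported without its background share invites readers to attribute all of it to the arrest.

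**Working it through.** **Plan's own figure.** The article gives no expected share of the norm population below the line, so there is nothing to reproduce.

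**Inputs.** From section 2.4: a cut-off at the age-matched norm mean minus 7, used for prevalence and incidence. Assumed, because the article does not give them: a between-person SD within an age group of 10 to 25 points, and the shape of the distribution.

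**Step 1. Share of the norm population meeting the rule, normal scores.** Share = P(X ≤ mean − 7) = Φ(−7/SD).

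| Assumed SD | −7/SD | Share |
|---|---|---|
| 10 | −0.70 | 24.2% |
| 12 | −0.58 | 28.0% |
| 15 | −0.47 | 32.0% |
| 20 | −0.35 | 36.3% |
| 25 | −0.28 | 39.0% |

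Even an SD of 8 gives 19.1%.

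**Step 2. Left-skewed scores bounded at 0 and 100 (beta distribution).**

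| Norm mean | Share over SD 10 to 25 |
|---|---|
| 65 | 24.0% to 36.5% |
| 70 | 23.7% to 34.6% |
| 75 | 23.3% to 32.0% |
| 80 | 22.7% to 29.1% |
| 85 | 21.7% to 25.5% |

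Rounding scores to the nearest 5 (means 70 to 80) gives 21.6% to 34.1%. Taking steps 1 and 2 together, the background share for SD 10 to 25 is about 22% to 39%.

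**Step 3. Does the proportion respond to a real deficit?** Suppose survivors are truly 10 points below the norm, with normal scores. Share = Φ((−7 + 10)/SD).

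- SD 15: Φ(0.20) = 57.9%, against 32.0% in the norm; excess 25.9 percentage points.
- SD 20: Φ(0.15) = 56.0%, against 36.3% in the norm; excess about 20 percentage points.

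So the proportion does rise, but more than half of the reported figure would be background.

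**Step 4. Do the planned exact intervals cover this?** With the 280 patients expected in section 3.2 and a proportion of 0.32, the approximate 95% half-width is 1.96 × √(0.32 × 0.68/280) = 0.055. The interval describes sampling error of about 5 percentage points. It says nothing about a background share several times larger.

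**Step 5. Incidence.** A simulation took a cohort with the norm's distribution. Each person had a fixed underlying level, and scores varied from visit to visit with an assumed between-visit correlation of 0.9 down to 0.6. Among those above the line at T0, the share below it at one or more of four follow-ups was 20.5% to 43.7% for SD 15 and 22.6% to 47.7% for SD 20. Nobody in the simulation deteriorated.

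**The case against.** - **The size rests on an unseen SD.** This stands. The norm source may report a spread, but the article does not. Under normality the share exceeds one third only when SD is above about 7/0.431 = 16. Under the skewed shapes it also needs a norm mean near 70 or below. With a mean of 75 to 80 the range is about 23% to 32%. A reader should not take any single percentage as established.
- **A reader might infer that the figures do not measure burden at all.** The documents do not support that. As step 3 shows, the proportion moves with a true shift, and it can be interpreted once the norm's own share is known.
- **A reader might infer that incidence would be mostly noise.** Step 5 does not show this. It gives what a stable cohort would produce under assumed correlations, not the fraction of survivors' incident cases that are spurious.
- **A reader might object that a 1-point move can create an incident case.** That is true of every threshold in section 2.4, including HADS, IES-R and MoCA, so it is no special defect here. The text states openly that the reference is the norm, so the incidence rule matches the prevalence rule and does not contradict it.
- **Quality of life is also analysed on a continuous scale.** It is, through the mixed models. They describe change over time among survivors. They neither compare survivors with the norm nor supply the missing background share.
- **This is not the main result.** Correct. The feasibility and acceptability thresholds in section 2.2 concern recruitment and retention, and the precision statement in section 3.2 concerns anxiety or depression ("in 25% of cardiac arrest survivors at 6 months from the event, with 5% precision and 95% confidence"). That limits the consequence without removing it.

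**Conclusion.** The point holds as one of interpretation. Section 2.4 turns a minimal important difference into an individual case line just below a population mean, uses it for prevalence and incidence, and plans no norm comparator. For an assumed SD of 10 to 25, about 22% to 39% of people with ordinary quality of life would be cases. That a substantial background share exists does not depend on one SD or on normality; its exact size does. The raw prevalence therefore cannot be read as burden due to cardiac arrest, and incidence partly counts random crossing of a fixed line. The recruitment and retention criteria are unaffected. The change is worth making because it is cheap and the outcome belongs to a stated aim.

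**What to change.** 1. **Main comparison.** At each visit, subtract the age-matched norm mean from each survivor's EQ VAS, report the mean of these differences with a 95% CI, and judge it against −7. This uses the 7 points as a difference in means and needs only the norm means that the plan already requires. Treating the norm means as known, the half-width with 280 patients would be 1.96 × 15/√280 = 1.8 points (SD 15) or 1.96 × 20/√280 = 2.3 points (SD 20). With 140 patients, the 50% retention threshold, it would be 2.5 or 3.3 points. Either is adequate for a comparison with −7.
2. **If the proportion is kept**, show it beside the share of the norm population expected below the same line. Use the norm source's spread if it gives one, and otherwise a stated SD range.
3. **Incidence wording.** Describe it as crossing the norm-based line, not as a decrease.

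Two further options are debatable and not required. A low-percentile cut-off needs the full norm distribution, which may not be available. Requiring a 7-point fall from the patient's own baseline relies on T0, an early post-arrest score, and would leave out patients who cross the line with a smaller fall.

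Cost: slightly more analysis and some rewording, with no new patient data. The reported burden will look smaller once the background share is shown.

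### The threshold for reduced quality of life uses a norm matched on age only; if that norm differs by sex, it can misclassify men and women and shift the prevalence

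*Protocol article*

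**What the plan says.** Section 2.4 (Statistical Methods) of the protocol article counts a patient as having reduced quality of life with an "EQ-5D-5L VAS score at least 7 points lower than the age-matched Italian general population mean". The 7 points are justified as "based on established minimal clinically important differences identified in chronic disease populations". Prevalence on this definition is to be estimated at every timepoint, with exact 95% confidence intervals.

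The incidence definition in the same section repeats the rule: "a decrease of ≥7 points from the age-matched normative mean on the EQ-5D-5L VAS for reduced quality of life". The rule therefore also decides who is free of the condition at baseline and so enters the incidence rate.

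Sex is mentioned in neither definition. It is recorded: section 2.3 states "Data collected will include demographic data (age, sex, etc" and so on. Later in section 2.4 it is one of the examples given for the mixed-effects models, "incorporating time and potential covariates (e.g., age, sex, comorbidities".

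**The concern.** A population norm stands in for the score a person would be expected to have without the illness. The plan applies that idea to age. A norm that averages men and women at each age is too low for one sex and too high for the other whenever their norms differ. The sex with the higher norm is then called reduced too seldom, and the other sex too often. Two consequences would follow.

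- A breakdown by sex would show a gap that comes from the reference value, even if men and women had lost the same amount of quality of life.
- The overall prevalence, and the at-risk set for incidence, would depend on how far the cohort's sex mix departs from that of the norm population.

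This would be a bias, so it would not shrink with more patients and the exact confidence intervals would not show it.

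**Working it through.** **What the article supplies.** It gives the 7-point margin and the age-only norm (section 2.4), sex as a collected item (section 2.3), and an expected cohort of about 280 (section 3.2). It gives no prevalence of reduced quality of life, no norm by sex, no sex mix and no VAS standard deviation, so there is no planned figure for this outcome to reproduce.

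**Yardstick.** The only planned precision is for anxiety or depression (section 3.2): "in 25% of cardiac arrest survivors at 6 months from the event, with 5% precision and 95% confidence". The formula n = 1.96² × p(1 − p)/d² with p = 0.25 and d = 0.05 gives 288. At n = 280 the half-width is 1.96 × √(0.25 × 0.75/280) = 5.07 points. The stated figure is reproduced to within 3%. It does not depend on the norm and serves only as a scale.

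**Assumptions.** None of these comes from the article.
- EQ VAS is normally distributed with SD 15 to 20.
- Patients lie 0 or 5 points below the norm for their own age and sex.
- The pooled norm is a 50:50 average of the two sexes.
- D is the norm difference between the sexes, 2 to 6 points, with D = 0 as control.
- The majority sex makes up 70 to 80% of the cohort; 50% and 90% are shown for comparison.

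**Quick approximation, patients 5 points below norm.**
- Shift of the effective norm = (majority share − 0.5) × D. Smallest: 0.2 × 2 = 0.4 points. Largest: 0.3 × 6 = 1.8 points.
- Change in prevalence = Φ((−2 + shift)/SD) − Φ(−2/SD), where −2 = −7 + 5.
- Smallest, SD 20: Φ(−0.080) − Φ(−0.100) = 46.8% − 46.0% = 0.8 points.
- Largest, SD 15: Φ(−0.0133) − Φ(−0.1333) = 49.5% − 44.7% = 4.8 points.
- The sign depends on which sex is in the majority. If it is the one with the higher norm, prevalence is understated; if the other, overstated.

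**Full mixture.** With deficit s and the pooled norm set to zero:
- higher-norm sex: P = Φ((−7 + s − D/2)/SD)
- lower-norm sex: P = Φ((−7 + s + D/2)/SD)
- under sex matching, both: P = Φ((−7 + s)/SD)

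Example with SD 18, s = 0, D = 4: 30.9% and 39.1%, against 34.9% for both under sex matching. The cohort figure, by share of the higher-norm sex:

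| Share | Age-only norm | Age-and-sex norm |
|---|---|---|
| 50% | 35.0% | 34.9% |
| 70% | 33.3% | 34.9% |
| 80% | 32.5% | 34.9% |
| 90% | 31.7% | 34.9% |

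Across SD 15 to 20 and s = 0 or 5:

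| D | Overall difference at 90% higher-norm sex (points) | Gap between the sexes at equal true deficit (points) |
|---|---|---|
| 0 | 0 | 0 |
| 2 | 1.5 to 2.1 | about 4 to 5 |
| 4 | 2.9 to 4.2 | about 7 to 11 |
| 6 | 4.3 to 6.2 | about 11 to 16 |

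At a 50:50 mix the overall difference is at most about 0.4 points, but the gap between the sexes remains.

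**The case against.** The case for leaving the definition alone is substantial.

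- **Clarity.** The definition is reproducible and is used the same way for prevalence and incidence. That stands: nothing is misstated.
- **Unseen source.** The effect exists only if the cited norm differs by sex within age. That stands too, and makes the point conditional: with D = 0 the two definitions agree at every sex mix.
- **Covariates.** A reader might infer that the plan contradicts itself by naming sex as a covariate for EQ-5D-5L while leaving it out of the norm. The article does not support this. The covariates are optional examples in models for score change and retention, not in the binary definition. By the same logic the norm would have to be matched on comorbidities as well.
- **No planned sex comparison.** The article plans descriptive prevalence, attributes none of it causally to the arrest, and specifies no comparison of men and women on this outcome. This limits the harm from the within-sex gap, although the overall figure can still move.
- **Size.** At the middle of the assumed ranges (D = 4, 75% of one sex, SD 17.5, deficit 5) the norm shifts by 0.25 × 4 = 1.0 point and prevalence by about 2.3 points. At a prevalence near 45% the 95% half-width is about 5.8 points with 280 patients and about 8.2 with 140, the number left at 50% retention. The shift is thus smaller than sampling error. It is still systematic, so the comparison reduces its importance without removing it.
- **Choice of target.** Sex matching gives men and women different thresholds for the same VAS score, and it would not remove real differences in outcome between them. That is right; the refinement addresses only the part due to the reference value.

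**Conclusion.** The point holds as a minor, conditional refinement. The rule ignores sex in both places although sex is available. If the norm differs by 2 to 6 points between men and women of the same age, 70 to 80% of the cohort is of one sex and the SD is 15 to 20, the overall prevalence moves by about 1 to 5 percentage points, and the error within each sex is larger. If the norms are equal, nothing changes.

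A reader might conclude that the reported prevalence will shift with the sex mix. The article does not support that, since it shows neither a sex difference in the norm nor the expected sex mix. Confidence that the effect is material is low. What justifies raising it is that the remedy is cheap, harmless if the norms are equal, and removes a bias invisible in the confidence intervals if they are not.

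**What to change.** Before analysis, check whether the cited Italian norm source tabulates EQ VAS by age and sex.

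- If it does, change both definitions in section 2.4, prevalence and incidence, to at least 7 points below the age- and sex-matched Italian general population mean.
- If it does not, keep the age-matched norm, report reduced quality of life by sex as well as overall, and state the limitation.

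The cost is a few words in two places and a lookup by sex. No new data are needed, because sex is already collected. The one dependency is that the norm source must give values by age and sex.
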